### Biological sample collection at South African sites to estimate prior ART exposure

For a subsample of South African study participants who are enrolled on the day of ART initiation or re-initiation who self-report as ART-naïve or not having been on treatment for a least 90 days, a dried blood specimen (DBS) will be collected from PREFER survey participants at some study sites. The objective of this component of the study is to add to the evidence base about the proportion and characteristics of the large group of clients who have prior ART experience but do not reveal this to healthcare providers. As these clients have, by definition, previously faced barriers to ART retention, understanding more about them is essential to improving early treatment outcomes.

Sites were chosen based on willingness of providers to create the dried blood spots after obtaining venous blood sample for routine ART initiation blood tests. Blood is drawn routinely as part of the standard of care ART initiation process in South Africa. DBS specimens will be extracted from the routinely collected blood samples drawn by existing clinic staff (nurses or phlebotomists), who are trained in safe and sterile collection techniques. For the study, a sample of 50μml will be extracted from an existing EDTA vacutainer tube with a capillary tube and placed onto a Whatman Protein 903 filter paper. A minimum of 3 dried blood spots will be completed for each patient. Specimens will be allowed to air dry for 2 hours after being taken, or according to assay instructions. Specimens will be covered with glycine weighing paper after drying. Collected, dried specimens will be stored in a -4°C freezer and be shipped in 6-weekly batches via courier to the University of Cape Town Division of Pharmacology, PK Laboratory for analysis. Specimens will be batch-screened for the presence of tenofovir diphosphate.

Participants who meet the inclusion criteria for this subsample (initiating or re-initiating ART and self-reporting as ART-naïve or not having been on treatment for HIV for at least 90 days) will be consecutively enrolled up to a maximum of 200 participants from all participating study sites combined. Enrollment in this subsample will begin when the consumables required for DBS creation have been procured and staff have been trained on standard operating procedures for creating a DBS. Consent for biological sample collection is included in the overall survey consent form.

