To analyze the DCE survey data collected before the FGDs, we will estimate the impact of each attribute on a participant’s choice using a conditional logit model and a random effects probit model. The DCE results will be triangulated with the survey and FGD finding to complement PREFER overall conclusions about client preferences.

For the analysis of prior ART exposure, the presence of TDF above 0.02μg/ml in blood samples will be considered as positive for previous ART use in the previous 3 months or as advised by the laboratory. We will report the proportion of those who have evidence of usage of TDF and, where possible, use the quantified measure to estimate frequency of ART usage, in the preceding 90 days. If sample size allows, we will also identify client characteristics associated with prior ART exposure, using survey responses and medical records.

The study results will be disseminated in several ways. The primary audiences for the results of this study are the South African National Department of Health and Zambian Ministry of Health and their partners, who will use the findings to improve retention in care during the early treatment period. In addition, we will use the results to inform the design of one or more new models of service delivery, which we expect to implement and evaluate during a later stage of this project. Many of the findings will also likely be of broader interest in South Africa and other countries and will be made as widely available as possible, through journals, websites, and conferences. Only aggregated, stratified data will be presented; it will not be possible to identify any individual patients from any of the results that are presented.

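### A blood spot with tenofovir above the cut-off is labelled previous ART use, although the assay cannot tell treatment from HIV prevention

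*Protocol article*

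**What the plan says.** The section on biological sampling in South Africa gives the aim as adding evidence on "the proportion and characteristics of the large group of clients who have prior ART experience but do not reveal this to healthcare providers". It tests clients who are "initiating or re-initiating ART and self-reporting as ART-naïve or not having been on treatment for HIV for at least 90 days", up to 200 in all. One analyte is named: "Specimens will be batch-screened for the presence of tenofovir diphosphate".

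The section Data analysis and dissemination fixes the rule that turns a result into a classification: "the presence of TDF above 0.02μg/ml in blood samples will be considered as positive for previous ART use in the previous 3 months", with the qualifier "or as advised by the laboratory". The next sentence reads "We will report the proportion of those who have evidence of usage of TDF" and adds that, where possible, the study will "use the quantified measure to estimate frequency of ART usage, in the preceding 90 days". Survey answers and medical records enter only afterwards, if numbers allow, to look for client characteristics associated with prior exposure.

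Neither pre- nor post-exposure prophylaxis is mentioned in the article. The Limitations section discusses under-reporting of earlier ART by self-report. It does not discuss a positive assay that has a source other than treatment.

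**The concern.** The rule treats exposure to one drug as evidence of treatment. A concentration above a cut-off shows that the drug was taken, but not for what purpose. A client who used tenofovir for prevention, then tested HIV-positive and truthfully reports never having been on ART, meets the criteria for the subsample and would be classed as having used ART. Because that client reported being naïve, the result would be read as non-disclosure.

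The proportion with undisclosed ART is the main product of this component, and the error pushes it upward. Testing more clients does not remove the bias, and a confidence interval does not show it. The same error carries into the quantified analysis, where the level is read as frequency of ART use. It also mixes people with no treatment history into any description of non-disclosers, and separating naïve clients from re-initiators is a stated purpose of the study.

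**Working it through.** The article gives no precision or error calculation for this component; 200 is only an enrolment cap. There is therefore no figure to reproduce, and the check is a sensitivity calculation.

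**Inputs**
- n = 200, the cap in the section on biological sampling. Treating all 200 as self-reported naïve is a simplification. The tested group also includes clients who disclose earlier ART, so the counts below are upper values for the naïve group.
- p = true proportion with undisclosed ART. Scenarios are 19% and 53%, the metabolite proportions that the Introduction cites for self-reported naïve initiators in two South African studies.
- q = share of clients without recent ART who have tenofovir from prophylaxis above the cut-off. The documents do not give it. Assumed range: 1% to 5%; it could be zero.

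**Formulas**
- Reported proportion = p + (1 − p)q
- False positives = n(1 − p)q
- Share of positives that are false = (1 − p)q / [p + (1 − p)q]

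**Results**

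| p | q | Reported | Upward shift (points) | False positives in 200 | Share of positives false |
|---|---|---|---|---|---|
| 19% | 1% | 19.81% | 0.81 | 1.6 | 4.1% |
| 19% | 2% | 20.62% | 1.62 | 3.2 | 7.9% |
| 19% | 5% | 23.05% | 4.05 | 8.1 | 17.6% |
| 53% | 1% | 53.47% | 0.47 | 0.9 | 0.9% |
| 53% | 2% | 53.94% | 0.94 | 1.9 | 1.7% |
| 53% | 5% | 55.35% | 2.35 | 4.7 | 4.2% |

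Example, third row: 200 × 0.81 × 0.05 = 8.1 false positives; true positives are 200 × 0.19 = 38; 8.1 / 46.1 = 17.6%.

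**Comparison with sampling error** (Wald 95% half-width, n = 200)
- p = 19%: 1.96 × √(0.19 × 0.81 / 200) = 5.4 points
- p = 53%: 1.96 × √(0.53 × 0.47 / 200) = 6.9 points

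Every shift in the table is smaller than the matching half-width. Of the scenarios tried, only q = 10% with p = 19% exceeds it (0.81 × 0.10 = 8.1 points), and that lies outside the assumed range.

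**Check on the choice of p.** The cited 19% and 53% are observed metabolite proportions and may already contain prophylaxis. If they are read as what the rule returns, the true proportion is (reported − q)/(1 − q). A reported 19% becomes 18.2% at q = 1% and 14.7% at q = 5%, so 4.3% to 22.4% of positives are false. A reported 53% becomes 52.5% and 50.5%, so 0.9% to 4.7% are false. The picture is similar.

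**The case against.** Several points on the other side are sound.

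- The rule has a cut-off that the laboratory may revise, so it is wrong to say that any trace of tenofovir counts. That stands. But moving the cut-off or the window does not identify the source of the drug.
- Taken alone, the sentence on reporting evidence of TDF use is neutral and close to the proposed remedy. That also stands. The defect is in the sentence before it, which equates the result with ART, and in the clause after it, which reads the level as frequency of ART use.
- A reader might infer that the article wrongly says all positives have already faced barriers to staying on ART. It does not. That remark concerns "clients who have prior ART experience but do not reveal this to healthcare providers", a group defined by actual earlier ART and not by the assay.
- A reader might also take every positive for a concealed restart. The tested group includes clients who openly report earlier ART but at least 90 days off it. For them a positive contradicts only the timing.
- The use of tenofovir for prevention is outside knowledge, and its frequency here is unknown. The documents therefore cannot show that even one client would be misclassified.
- The survey form is a supplementary file not shown and may ask about prophylaxis. Even so, the rule as stated makes no use of such an answer.
- Downstream harm is limited. The analysis of characteristics is conditional on sample size, and the Limitations section says the subsample is too small to stratify by patient or facility characteristics.

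**Conclusion.** The point holds as a matter of labelling and classification. The article states a rule that converts tenofovir above a cut-off into previous ART use, with no step that separates treatment from prevention. The resulting error in the proportion with undisclosed ART can only be upward.

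Its size cannot be derived from the documents. Under the assumed 1% to 5%, it is about 2 to 8 clients in 200 at a true prevalence of 19% and about 1 to 5 at 53%, and it stays within sampling error. A reader might apply 5% to all 200 and conclude that 10 of 48 positives (21%) are wrong. On that scenario only the 162 clients without ART can be false positives, which gives 18%. The documents do not support a claim that the result would be seriously distorted; they support correcting the definition.

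The reverse error deserves a sentence as well. With one analyte and a three-month window, a negative result does not exclude earlier ART or a regimen without tenofovir. The article does not claim that it does.

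**What to change.** In Data analysis and dissemination:

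- Define a positive as recent tenofovir exposure, and describe the quantified level as frequency of tenofovir use.
- Among clients who self-report as naïve, label a positive as undisclosed prior ART only when neither the survey nor the medical records show prophylaxis in the look-back. Report positives explained by prophylaxis as their own category.
- Report separately the positives among clients who disclose earlier ART but state at least 90 days off treatment.

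In Limitations, add that a positive cannot identify why the drug was taken, and that a negative does not exclude earlier or tenofovir-free ART.

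The cost is one extra table row for the prophylaxis category, a split of positives by self-reported history, and at most one question for the subsample if the survey form does not already ask it. The headline proportion may fall slightly. According to Current status of the study, blood sampling had not begun when the manuscript was first submitted, so at that point the question could still have been put to the whole subsample.

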### Limitations

We anticipate that the PREFER study will have a number of limitations. First, the target sample size is small, in terms of both number of study sites and number of participants, and generalizability to districts and provinces not included in the survey will require caution. Second, survey participants will provide responses about their experiences up to 6 months after ART initiation, creating the possibility of recall bias for questions pertaining to HIV testing and other pre-ART events. Third, we will largely rely on participant self-report to determine prior ART use. Several studies have demonstrated underreporting of prior ART use by self-report which could result in exposure misclassification for analyses stratified by prior treatment status. While we plan to do dried blood sampling to measure ART metabolites for prior ART exposure, the subsample who will be tested will be too small to stratify by patient or facility characteristics. Fourth, as we can only enroll participants actively participating in ART care at health facilities, the study will not capture the experiences and perceptions of individuals who have already disengaged from care. While we will be able to observe re-initiators, those who have not returned to the initiating facility will not be enrolled, potentially limiting our understanding of those who have disengaged from care. Fifth, we will utilize routinely collected EMR data to ascertain participant ART retention outcomes at 6 months after ART initiation. While efficient in terms of resources, this approach is limited to data observed at the initiating facility and will not observe participants accessing care at other facilities. Silent transfers such as these may result in outcome misclassification among some classified as disengaged.

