## Introduction

Rapid, same-day, and community-based initiation of antiretroviral therapy (ART) for HIV has shifted the challenge of achieving optimal outcomes in HIV treatment onto retention in care after a patient has started ART. The highest risk for loss from care consistently remains a patient’s first six months after ART initiation
^
1
^. Dubbed the “early retention” period
^
2
^, this interval accounts for roughly three quarters of all first-year attrition from HIV programs in sub-Saharan Africa
^
3
^. In South Africa, 26% of patients were lost to follow up by 6 months after initiation in a recent trial of a case management intervention
^
4
^, and attrition was 35.6% by 6 months in a recent observational study
^
5
^.

Patient characteristics and service delivery characteristics both contribute to high attrition during the early treatment period
^
1
^. After the World Health Organization (WHO) began recommending universal treatment access in 2016, the median CD4 count of new ART initiates rose substantially, reflecting the much higher proportion of asymptomatic, “healthy” patients than in the past
^
6
^, despite a fairly consistent minority of a quarter to a third continuing to present with very low CD4 counts
^
7,
8
^. The proportion of patients who are re-initiating ART after previously interrupting care is also climbing. A recent modeling exercise estimated that in 2020, fully 58% of those who tested positive for HIV were already aware of their positive status
^
9
^ and thus may have declined an earlier opportunity to start or remain on treatment. Two small studies in South Africa identified ARV metabolites—evidence of recent exposure to ARV medications—in 53% and 19% of self-reported naïve ART initiators in Limpopo and KZN provinces, respectively
^
10,
11
^. Individuals who know their HIV-positive status but are not on ART likely face multiple barriers to starting treatment; those who both know their status and have already started and stopped ART at least once (re-initiators) may require additional support to remain in care once they re-initiate care.

The service delivery landscape has transformed at many points in the HIV treatment cascade in recent years, most notably through the introduction of rapid and same-day ART initiation for those not yet on treatment
^
12
^ and the development of patient-centred differentiated service delivery (DSD) models for those already established on ART for at least 6 months
^
13

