^. Neither same-day initiation nor most current DSD models, however, offer solutions for patients during the first six months after initiation
^
14
^. The model of care for the early treatment period that is offered to most newly-initiating and re-initiating patients has evolved little from its original outlines, though COVID-19 restrictions precipitated some reductions in required numbers of clinic visits and increases in dispensing intervals
^
15
^.

A first step in designing new models of care for the early treatment period is to gain a comprehensive understanding of patients’ needs, concerns, resources, and preferences for service delivery during this period. Treatment and retention in the first 6 months after ART initiation could be improved if patients were triaged to receive more or less support based on a combination of known risks to retention in care and patient preferences for how little or how much interaction, and what kinds of interaction, with the health system are desired.

In the PREFER study, we will use a sequential mixed-methods approach to survey a sample of patients in South Africa and Zambia at various points between months 0 and 6 after ART initiation to develop a detailed profile of different groups of patients who may be best served by different models of care. The specific objectives of the study include describing the characteristics and preferences of new and re-initiating ART clients, exploring their concerns in depth through focus groups, identifying associations between client characteristics and early treatment outcomes, and assessing differences between naïve and non-naïve treatment initiators.

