### Medical record review for outcomes and resource utilization

Using identifiers collected as part of the structured questionnaire, we will also collect follow up data from routine medical records for the period from each participant’s initial data entry (first presentation for testing or care) to 12 months after study enrollment, with an additional round of medical record data collection up to 24 months after study enrollment in South Africa. The objective of this component of the study is to describe early treatment outcomes and, using data from the survey, identify associations between client characteristics and their outcomes, in order to better match early treatment interventions with client needs.

Medical record data will be drawn from Tier.Net in South Africa and Smartcare in Zambia, paper records and registers maintained at the study sites, and other databases, such as South Africa’s National Health Laboratory Services database, to ascertain whether patients are retained in care during the first 6 months on ART. We will collect data on HIV treatment history and current engagement, medications dispensed, laboratory tests performed, comorbidities, and other healthcare provided by the site and recorded in the EMR during the study period. We note that the EMRs in both countries are largely limited to HIV care; they may capture data on tuberculosis and other conditions but generally do not contain information about services provided by other departments within the clinics.

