### Data analysis and dissemination

We will first create a descriptive summary of the demographic and clinical characteristics of participants enrolled in the study and responses to each question using frequencies and simple proportions for categorical variables and medians with interquartile ranges for continuous variables. We will then stratify these baseline survey responses by site characteristics, time on ART, self-reported naïve v non-naïve treatment status, and/or patient characteristics such as age and sex, as data allow. Data will not be pooled across countries, but differences in results by country will be noted and discussed.

Utilizing follow up data collected from patient medical records, we will conduct a crude analysis reporting simple proportions with 95% confidence intervals of patients disengaging from care, defined as missing a scheduled clinical or medication pickup visit during the first 6 months after treatment initiation by more than 28 days. Next, we will compare the proportions of patient disengaged from care by key variables including age, gender, clinical stage at ART initiation, site characteristics, time on ART, and naïve v non-naïve treatment status.

If enrollment numbers allow, the analysis will include a simple unadjusted comparison of outcome groups (retained or disengaged) with respect to baseline predictors of outcomes. Potential predictors include demographic and clinical variables and geographic and facility-level factors (urban vs rural setting, facility type). Using a log-linear regression model, we will next estimate crude risk ratios and crude risk differences and their corresponding 95% confidence intervals. If any important differences are observed, we will proceed with an adjusted model. Should crude stratification techniques reveal potential effect measure modification, these analyses will not be adjusted but rather reported as stratified output.

For the FGD output, we will conduct a content analysis of the qualitative data using the Framework Method
^
20
^. We will use a combination inductive-deductive approach wherein most codes will be identified
*a priori*, aligned with the FGD guide and literature, but the coding process will allow for additional codes to emerge to form a final analytical framework. Data will be charted, summarized, and quotations will be presented to illustrate key points when appropriate. Results will be presented stratified by country and urbanicity of sites.

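### The naïve v non-naïve grouping rests largely on self-report, and the planned treatment-history records are not assigned to checking it

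*Protocol article*

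**What the plan says.** The Introduction lists among the objectives "assessing differences between naïve and non-naïve treatment initiators", and the Abstract and the Conclusions repeat the aim of separating the barriers of the two groups.

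Two planned analyses in Data analysis and dissemination use the grouping:
- Survey responses are stratified by "self-reported naïve v non-naïve treatment status".
- Disengagement is compared by several variables, ending with "site characteristics, time on ART, and naïve v non-naïve treatment status". Here the source of the status is not named. Risk ratios and risk differences for baseline predictors follow, numbers permitting.

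The Limitations section states the source: "we will largely rely on participant self-report to determine prior ART use". It adds that prior use is known to be under-reported, "which could result in exposure misclassification for analyses stratified by prior treatment status", and that the DBS subsample is too small to stratify.

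On how common hidden prior use may be, the Introduction reports metabolites "in 53% and 19% of self-reported naïve ART initiators in Limpopo and KZN provinces".

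On the data available, Medical record review for outcomes and resource utilization says: "We will collect data on HIV treatment history and current engagement, medications dispensed, laboratory tests performed". Extraction reaches back to the participant's first contact for testing or care. The sources are the national electronic record systems and paper records in both countries and, in South Africa, the national laboratory database. The stated purposes are outcomes, their predictors and retention. DBS testing is limited to at most 200 people at some South African sites.

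**The concern.** The grouping variable for a stated aim is one that the article itself expects to be under-reported, and in one direction: people with earlier ART present as naïve. The naïve group then becomes a mixture, while the non-naïve group stays comparatively clean. If hidden re-initiators behave like disclosed ones, the two groups are drawn together. The study could then report similar barriers and similar disengagement because the groups overlap, not because the clients are alike.

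The results are meant to inform new service-delivery models, so a falsely small contrast has consequences. The limitation is disclosed, but the only remedy considered is the small DBS subsample. The record data, planned for every participant, would bear on the same question and are not given that job.

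**Working it through.** **The plan's own figures.** The article states no sample size, effect size or power for this comparison. Its minimum targets reproduce: 18 sites × 50 = 900 (South Africa) and 12 × 50 = 600 (Zambia).

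**Inputs**
- f, the share of self-reported naïve clients with prior ART: 0.19 and 0.53 (Introduction). Both come from small South African studies of self-reported naïve initiators. KZN (19%) is a study province; Limpopo (53%) is not (Table 1).
- p0, the disengagement risk in truly naïve clients: 26%, or 35.6% as an alternative. The Introduction gives these as 6-month attrition in all patients of two South African studies; using them for naïve clients is an assumption.
- RR, the true risk ratio of disclosed re-initiators v truly naïve clients: 1.25 and 1.5 (assumed).
- k, the risk of hidden re-initiators relative to truly naïve clients (assumed; varied in step 2).
- Self-reported non-naïve clients are taken as truly non-naïve.

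**Formula.** Risk in the self-reported naïve group = p0 × [1 + f(k − 1)]. Hence observed RR = RR / [1 + f(k − 1)], and observed RD = p0 × [(RR − 1) − f(k − 1)].

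**Step 1: hidden re-initiators carry the disclosed re-initiators' risk (k = RR).** Observed RD is then (1 − f) × true RD.

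| True RR | f = 0.19 | f = 0.53 |
|---|---|---|
| 1.25 | 1.25/1.0475 = 1.19 | 1.25/1.1325 = 1.10 |
| 1.5 | 1.5/1.095 = 1.37 | 1.5/1.265 = 1.19 |

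With p0 = 26% and RR 1.5, the true RD of 13.0 points becomes 0.81 × 13.0 = 10.5 or 0.47 × 13.0 = 6.1. With p0 = 35.6%, 17.8 points become 14.4 or 8.4.

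**Step 2: their risk differs (RR held at 1.5).**

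| k | f = 0.19 | f = 0.53 |
|---|---|---|
| 0.8 | 1.5/0.962 = 1.56 | 1.5/0.894 = 1.68 |
| 1.0 | 1.50 | 1.50 |
| 1.5 | 1.37 | 1.19 |
| 2.0 | 1.5/1.19 = 1.26 | 1.5/1.53 = 0.98 |

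Attenuation is therefore one scenario, not a certainty.

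**Step 3: error over all participants.** The cited percentages apply only to the self-reported naïve. If 50%, 70% or 90% of participants report being naïve (assumed), the misclassified share of everyone is:
- 0.5 × f = 9.5% to 26.5%
- 0.7 × f = 13.3% to 37.1%
- 0.9 × f = 17.1% to 47.7%

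**Step 4: what DBS can supply.** Coverage in South Africa is at most 200/900 = 22% at the minimum target and 200/2,500 = 8% at the maximum; it is nil in Zambia. The half-width for f is 1.96 × √[f(1 − f)/n]. With n = 200 self-reported naïve clients it is ±5.4 points at 19% and ±6.9 at 53%; with n = 100, ±7.7 and ±9.8. The smaller n matters because the subsample also admits people who report earlier treatment but none for at least 90 days. So DBS can estimate f usefully but cannot classify the cohort.

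**The case against.** Several objections carry weight.

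- **The cited rates are not PREFER's.** A reader might infer that the article says self-report is wrong in 19% to 53% of cases. It does not. It reports two small studies, neither in Zambia, and the larger figure is from a province outside the study. PREFER also asks in private, through a research assistant, with a dedicated treatment-history section, so its own under-reporting rate is unknown. This stands.
- **Bias toward no difference is not guaranteed.** It needs hidden re-initiators to resemble disclosed ones, and nothing in the article supports or refutes that. This stands; step 2 of the working shows the range.
- **The other data were not in hand.** A reader might suppose that they had already been collected. Under Current status of the study, record review and biological sampling had not begun. This stands, and it means that a rule could be set before those data existed.
- **DBS cannot reclassify people.** Folding it into an any-evidence definition looks attractive. But it covers at most 200 day-of-initiation clients at sites chosen for provider willingness, and TDF reflects about 3 months. Classification would then differ by site and by time on ART, both comparison variables. A negative result does not show naïveté. This stands.
- **Records are imperfect.** The article says its record-based outcomes see only the initiating facility. Treatment history may share that limit, and exposure and outcome errors from one source could be correlated. This argues for showing both groupings, not for self-report alone.
- **The study is descriptive, the limitation is disclosed, and details may sit in an unseen document.** This does not remove the point. The article itself fixes self-report as the main basis and plans comparisons on it. The word largely leaves room for other sources, but none is named.

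**Conclusion.** The point holds in limited form. The article fixes self-report as the main basis for a comparison that is one of its aims, cites evidence that self-reported naïve groups can be substantially mixed, and assigns none of the planned record data to checking the grouping.

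If hidden re-initiators carry the disclosed re-initiators' risk and disclosed re-initiators are correctly classified, the risk difference shrinks by 19% at the KZN figure and by 53% at the Limpopo figure. The KZN figure is the only one from a study province. If the first assumption fails, the bias may be smaller, larger or in the other direction.

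The documents do not support a claim that this study's classification is wrong at those rates, that the comparison must be biased toward the null, or that the available data could fully correct it. Records can correct it in part, and DBS can inform a sensitivity analysis in South Africa.

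**What to change.** In Data analysis and dissemination:

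1. Add a record-augmented grouping. A participant is non-naïve if self-reported so, or if records show ART dispensing, an ART start or on-treatment laboratory monitoring dated before the current initiation. Apply one rule to all participants within each country. State that the national laboratory database contributes in South Africa only.
2. Report it beside the self-report grouping, cross-tabulate the two by country, and repeat the disengagement comparison under both. Name the source of status for each analysis.
3. Do not use DBS to reclassify individuals. In South Africa only, take the DBS-positive share among tested self-reported naïve clients, with its confidence interval, as a lower bound on misclassification in the tested group, because the TDF window is about 3 months. Use it in a quantitative bias analysis of the risk ratio and risk difference, varying both f and the assumed risk of hidden re-initiators as in the working.

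The cost is extra linkage and coding of data already planned for extraction, plus one sensitivity analysis; no new participant contact is needed. The drawback is that records may miss care at other facilities and their completeness may differ by country, so neither grouping should be presented alone.
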